## Background

Across the developed and developing world the population is ageing. In Australia it is predicted that, compared to 2005 the proportion of the population over 65 years of age will increase from 13% to 24%, by 2036 [1]. With this increase, the demand on Emergency Department (ED) services by older persons living in the community or in residential aged care facilities (RACF) will increase [1–3]. A systematic review of 27 studies from around the world has demonstrated that the rate of transfer to EDs from RACFs is 0.1–1.5 transfers per RACF bed/year [4].

As a result of this ageing of the population it is imperative that the health care system develop safe models of care (MOC) that span both the community and hospital health care sectors. While the ED is uniquely designed to care for the critically ill or injured, it is often a suboptimal environment for the provision of care to the frail, older person [5, 6]. Prior research shows that older persons who develop an acute illness or who have an acute exacerbation of a chronic condition, have complex medical needs and the doctors and nurses who manage their initial care in the ED often have limited experience in geriatric medicine [7, 8]. Several studies have shown that this situation leads to: under-triage; higher rates of admission; delayed and fragmented care; longer stays in the ED; and unnecessary investigations and invasive interventions [9–19]. For patients from RACFs this is particularly true. During admission to hospital, patients from RACFs are at high risk of complications such as delirium, urosepsis, falls and death [20–22]. Patients from RACFs who develop an acute illness or an exacerbation of a chronic condition also suffer high rates of re-presentation to the ED and subsequent re-admission to hospital [2, 10, 12, 14].

Several studies indicate that a large percentage of frail older persons living in the community or RACFs express a preference for treatment in their home if appropriate [23, 24]. Despite this, approximately 60% of ED presentations lead to hospital admission [25, 26]. In an attempt to keep frail older persons at their place of residence during an acute illness, several MOC have been designed and tested. Broadly, the different MOC are divided into those that: i) provide in-home care or outreach of services from one service to another [12, 24, 27, 28]; ii) provide prioritisation or geriatric focused care in the ED [29–32]; or iii) support or enhance primary care [28, 33].

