### Setting

This study is set on the Sunshine Coast of Queensland, Australia. In Australia, the current percentage of people aged 65 years and over accounts for around 14% of the population [1]. On the Sunshine Coast this percentage is expected to increase to 17% by 2031 [36]. The study will be conducted in the Nambour General Hospital, situated in the Sunshine Coast and Hospital Health Service (SCHHS). Nambour General Hospital is one of four public hospitals in the SCHHS. NGH is the base hospital containing 373 beds and the three secondary hospitals have a combined total of approximately 531 beds. All four hospitals have an ED where both adults and children are treated. The study ED has an annual presentation of 52,410 patients; 18% of whom are over the age of 70 years [36]. Locating the research in the SCHHS will provide evidence of the effectiveness and feasibility of this MOC in a regional setting.

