### Intervention

GEDI is a nurse-led, physician-championed innovative MOC that aims to reduce frail older person living in the community or RACF ED length of stay and streamline service delivery by maximising the provision of care during the patient’s ED journey. GEDI clinical nurses (CN) have a minimum of five years post registration experience and specialist expertise and/or education in both emergency nursing and care of the older person. Their role focuses on case-managing frail older persons living in the community or RACF in the ED facilitating rapid access and coordination of care through ED, hospital and community services.

There are 2.4 full time equivalent (FTE) GEDI CNs and a 0.8 FTE Clinical Nurse Consultant (CNC) employed by the ED. They cover the ED from 0700 to 1730 Monday to Friday and 0700 to 1530 on weekends. The GEDI CNC oversees the CN role, providing education, leadership, managerial oversight of the service and clinical support where needed. An ED physician provides medical leadership and together with the CNC they are responsible for research and administration.

In the ED, the GEDI team will provide early, rapid, targeted geriatric assessment of frail older persons living in the community or RACF presenting to the ED and, through careful inter-facility and interdisciplinary, management and planning, aim to prevent unnecessary admissions to hospital. In addition, the GEDI CNs provide a single point of contact for ED and RACF staff who may be having difficulty managing an older person with an acute illness. Table 1 outlines the elements included in the GEDI roles. The importance of the ED clinical experience required for the GEDI role relates to the need for GEDI CNs to optimise communication; multitask within a chaotic, fast-paced clinical environment; and be familiar with the staff, clinical pathways and protocols.

**Table 1 Tab1:** GEDI team responsibilities

GEDI Clinical Nurse Consultant	GEDI Clinical Nurse	GEDI Physician
Clinical responsibilities		
▪ Collaborative partnership with physician-champion to develop evidenced based guidelines specific to the needs of the geriatric patients and clinicians in the ED	▪ Works collaboratively with all ED staff	▪ Clinical resource and expert in geriatric emergency medicine

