##### Data collection

Data extraction will occur retrospectively via medical records audit of coded state based Health Service databases, namely Emergency Department Information Service (EDIS; Healthcare Group, CSC)® and Hospital Based Corporate Information System (HBCIS; iSoft). SCHHS Health Statistics unit provides linking of the EDIS, HBCIS and financial data providing raw data on all presentations to the ED and those admitted to hospital. The raw data will subsequently be manually cleaned to identify RACF residents based on their home addresses. This is important as RACFs often have independent living community residents at their facilities who needed to be excluded from this cohort. Independent variables that will be used to describe the sample and used to build multivariable models for outcomes are:Demographics - Age, Sex, postcodeDate and time of presentationClinical diagnosis – reason for presentation and ICD-10 code/categorySeen by GEDI team – Yes/NoAustralasian Triage Score [40]Adult Deterioration Detection System Score [41]Next of Kin/Substitute decision maker/Enduring Power of Attorney detailsTime to referral from ED arrivalTime to disposition from ED arrival

Outcome variables collected will be:Disposition - discharged home, moved to short stay area, admitted, diedED LoS – in minutesHospital LoS – in daysAll cause in-hospital mortality within 30 days of ED presentationED Re-presentations in 72 h and 28 daysTime to ED re-presentation within 28 days

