##### Data analysis

Descriptive statistics will be used to describe the intervention and control groups including frequencies, percentages, appropriate measures of central tendency and distribution. We will use survival analysis to jointly model length of stay and disposition, with the four destinations as competing risks. We will use survival analysis for ED representations with out-of-hospital mortality as a competing risk. All models will adjust for the patient level factors of gender, age, triage score, season, day of the week and time of presentation. Pre-post designs are vulnerable to confounding by other changes over time that may be attributed to the intervention [39]. To control for this, we will include a linear trend (based on date) in all models to account for gradual changes that are not captured in the individual variables, e.g., experience of healthcare workforce. We will also adjust for season using a sinusoid with an annual cycle to control for the winter peak in morbidity [42]. The survival analyses will use Cox models and we will check the proportional hazards assumption. The models’ residuals will be checked for outliers and correlation over time. We will calculate Cook’s influential statistic and examine relatively large outliers. We will calculate the variance inflation factor and remove variables with a score above five on the basis that they are co-linear. The key outcome will be the mean effect of the intervention together with 95% confidence intervals. The results will be reported using the Strengthening the Reporting of Observational Studies in Epidemiology (STROBE) guidelines [43].

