##### Data analysis

A multivariate cost function will be estimated to determine average cost per patient, for before- and after-GEDI MOC scenarios. The function takes into account important determinants of individual cost such as age, severity, length of stay and procedures received while in the ED. In the cost effectiveness analysis, we will estimate the average difference in number of admissions for the before- and after-GEDI scenarios. The number of avoidable admissions will be converted to cost savings using the results of the cost analysis above, and compared against the implementation cost for the GEDI MOC. If the cost savings is larger than the implementation cost, the GEDI MOC can be viewed as cost effective.

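### Admission is scored only as the disposition of each ED visit, so the admission result cannot separate prevented from postponed admissions

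*Protocol article*

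**What the plan says.** The Protocol article lists hospital admission rates among its outcomes under Study aims and again under Study design. Study 1, Data collection, gives the outcome its working form: a disposition for each ED presentation, with four categories, one of which is admitted. Study 1, Data analysis, then fixes the model, which is to "jointly model length of stay and disposition, with the four destinations as competing risks".

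Returns are handled in a second model: "We will use survival analysis for ED representations with out-of-hospital mortality as a competing risk". The event there is the return itself. The listed return outcomes are re-presentation at 72 h and 28 days and time to re-presentation. None is split by whether the return ended in admission.

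On the data, "SCHHS Health Statistics unit provides linking of the EDIS, HBCIS and financial data". The extract is to cover every ED visit as well as inpatient stays. The article does not say whether each presentation or only an index presentation is the row for analysis.

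The Intervention section says the team will "aim to prevent unnecessary admissions to hospital". In Study 3, Data analysis, "The number of avoidable admissions will be converted to cost savings", and these savings are compared with the implementation cost to decide whether GEDI is cost effective.

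**The concern.** GEDI acts at the point where the ED decides between home and ward. In the planned model a discharge home closes that visit's contribution to the admission outcome. If the person comes back some days later and is admitted, no listed outcome links that admission to the earlier discharge. The admission result therefore mixes admissions that never happened with admissions that happened later.

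Deferral is plausible on the protocol's own account: its Background describes high rates of ED return and re-admission among residents of aged care facilities. What is at stake is the claim that GEDI prevents admissions and, depending on how Study 3 counts, the savings credited to it.

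**Working it through.** The article gives no sample size, power or expected admission effect, so there is no planned figure to reproduce. The check asks what deferral alone does to the admission rate.

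**Inputs**
- Baseline admission p = 60%. Background: "approximately 60% of ED presentations lead to hospital admission". This is a literature figure, not this ED's own rate.
- Visits per year N = 52,410 × 0.18 = 9,434. Setting: "The study ED has an annual presentation of 52,410 patients; 18% of whom are over the age of 70 years".
- Number deferred and share later admitted: assumptions.

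**Step 1. Five per 100 visits deferred, all later admitted (true fall zero)**
- Every visit is a row: admissions stay at 60, visits rise to 105, and 60/105 = 57.1%, a false fall of 2.9 points.
- Index visits only: (60 − 5)/100 = 55.0%, a false fall of 5.0 points.
- Admission at the index visit or on a return within 28 days, per index visit: 60/100 = 60.0%, no false fall (returns assumed to occur within 28 days).

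**Step 2. Only a share r of the five return and are admitted**

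Every-visit rate = (60 − 5 + 5r)/(100 + 5r). Index-only rate = 55% throughout. True fall = 5(1 − r) points.

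| r | Every-visit rate | Apparent fall | Index-only fall | True fall |
|---|---|---|---|---|
| 1 | 57.1% | 2.9 | 5.0 | 0 |
| 0.5 | 56.1% | 3.9 | 5.0 | 2.5 |
| 0.25 | 55.6% | 4.4 | 5.0 | 3.75 |

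At r = 0.25 the overstatement is about 0.7 points (every visit) or 1.25 points (index only).

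**Step 3. Range over the share x of admissions deferred, all later admitted**

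Index only: p(1 − x). Every visit: p/(1 + px).

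| x | Deferred per 100 visits | Index only | Every visit |
|---|---|---|---|
| 2% | 1.2 | 58.8% | 59.3% |
| 5% | 3.0 | 57.0% | 58.2% |
| 10% | 6.0 | 54.0% | 56.6% |
| 20% | 12.0 | 48.0% | 53.6% |

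Step 1's five per 100 visits is 5/60 = 8.3% of admissions. At x = 10%, baselines from 40% to 70% give false falls of 4.0 to 7.0 points (index only) or 1.5 to 4.6 points (every visit).

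**Step 4. Size against sampling error**

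SE of a difference of two proportions = √(2 × 0.6 × 0.4/9,434) = 0.71 points. At x = 5% the chance of a nominally significant false fall (two-sided 0.05) is about 99% (index only) or 69% (every visit). At x = 2% it is about 39% or 17%. These figures are unadjusted and treat visits as independent. They are not results for the planned adjusted Cox models.

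**Step 5. The opposite direction**
- Suppose 2012 has 5 returns per 100 index visits that end in discharge, and GEDI prevents them. With every visit a row, the rate goes from 60/105 = 57.1% to 60/100 = 60%, an apparent rise of 2.9 points with admissions unchanged.
- Suppose instead those 5 returns ended in admission. The every-visit rate goes from 65/105 = 61.9% to 60%, a fall of 1.9 points where the true fall per index visit is 5. Index only shows no change.

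**The case against.** Four points on the other side carry weight.

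**Return admissions may still be counted.** A reader might infer that every postponed admission is scored as avoided. That is literally so only if index visits alone are analysed. If every presentation is a row, the return admission is counted at its own visit, the total stays at 60 in the example, and only the denominator grows. The article does not state the unit, and an article may leave that to the full protocol. The rate is distorted either way, by different amounts.

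**The bias does not always favour GEDI.** A reader might infer that it must. Step 5 shows otherwise: GEDI includes discharge planning and communication with primary care, and preventing returns can hide a benefit or show as harm.

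**Re-presentation would give a warning.** Five extra returns per 100 index visits, if within 28 days, is a 5-point rise. Its SE is at most √(2 × 0.25/9,434) = 0.73 points, so the signal is at least 5/0.73 = 6.8 SE, against about 4 SE (2.9/0.71) for the every-visit artefact. It would therefore be wrong to say that the plan is blind to deferral. What remains is that this outcome mixes returns ending in admission with all others, and leaves the admission estimate uncorrected.

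**Study 3 need not be misled.** It speaks of cost per patient and of a difference in the number of admissions. Costs summed per patient over the year would include the return and its admission, and a plain count over all visits is unchanged by deferral. The document does not support saying that Study 3 is wrong as written. It is affected if either quantity is taken from index visits or averaged per presentation.

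The headline example also assumes that everyone deferred is later admitted. At a 25% share the every-visit error is about 1 SE.

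**Conclusion.** The point holds in limited form. As defined, the admission outcome cannot tell prevention from postponement, and no other listed outcome supplies the correction. In the illustration the false fall is 2.9 points with every visit a row, or 5.0 points on index visits only. It shrinks to about 0.7 or 1.25 points when a quarter of those deferred return and are admitted. These sizes rest on a 60% baseline taken from the Background and on assumed deferral and return shares.

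The direction depends on what GEDI does to return visits. The effect on Study 3 is conditional on its counting unit. At-visit disposition remains a legitimate measure of the decision that GEDI is meant to influence; the weakness is that it stands alone.

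**What to change.** 1. Keep the at-visit competing-risks model as planned.
2. Add a co-reported outcome per index presentation, defined as a presentation with no ED visit in the previous 28 days: inpatient admission at that visit or through an ED return within 28 days, derived from the planned EDIS-HBCIS linkage. Report the adjusted before/after risk difference.
3. In Study 3, base avoided admissions, and ED plus inpatient cost, on the same 28-day episode.

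The cost is small: one derived variable and a few sentences of analysis wording, with no new data source. There are three downsides. There are fewer rows, because returns within 28 days are folded into their index visit. Identifying index visits needs a 28-day look-back extract before 1 January 2012 and before 1 September 2015, or trimming the first 28 days of both periods. Some admissions within the window will be unrelated to the index visit and will dilute the contrast; requiring admission through an ED return keeps out planned direct admissions.

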## Methods/design

### Study aims

The aims of the Geriatric Emergency Department Intervention (GEDI) MOC evaluative research project are to:Test the efficacy of the GEDI MOC by comparing the outcomes of all people aged 70 years or older who presented to a South East Queensland ED before the implementation of the GEDI MOC with those in the 12 months following implementation. Outcomes measured will be: rates of ED representation within 72 h and 28 days, mortality, ED and hospital LoS, time to referral, time to disposition and hospital admission rates;Describe and explore the structures and processes required for the effective delivery of the GEDI MOC;Conduct an economic evaluation of the GEDI MOC.

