▪ Develops and maintains enhanced communication strategies related to ED staff, RACF staff, Nurse Practitioner (NP), community services, paramedic staff and general medical practitioners (GPs).	▪ Enhanced communication by providing a dedicated single point of contact within the ED for RACF staff, NP, community services, paramedics and GPs to obtain support and advice regarding optimal care and management of acutely unwell or injured frail older person or RACF resident	▪ Facilitates interdisciplinary discussions and establishes clinical hospital wide networks
▪ Develops and upskills CNs in use of rapid assessment of frail older persons or RACF residents	▪ Rapid assessment and management of frail older persons or RACF resident including nurse initiated analgesia and investigations	▪ Identify information to be sourced by the GEDI CN relevant to ED medical officers
▪ Develops evidence based clinical care algorithms for common problems experienced by RACF residents within the ED	▪ Provides evidence based clinical care for older persons in the ED in collaboration with the primary nurse	▪ Provide education for emergency staff, promoting informed decision making and best practice
▪ Provision of a consultative service for patient centred care of the frail older person or RACF resident within the ED	▪ Provision of a consultative service for patient centred care of the frail older person or RACF resident within the ED	
▪ Develops systems and upskills CNs to undertake direct referral to Geriatricians and rapid consultation pathways with other medical service streams	▪ Direct referral to Geriatricians and rapid consultation pathways with other medical service streams	
▪ Develops systems to facilitate pre-hospital communication with the RACF, GP, NP and Ambulance service, facilitating appropriate transfer decision making and early arrival triage	▪ Pre-hospital communication with the RACF, GP, NP and Ambulance service, facilitating appropriate transfer decision making and early arrival triage	
	▪ Liaison with hospital acute-care substitution services such as the Hospital in The Home and palliative care services	
Administrative responsibilities		
▪ Collaborative partnership with physician-champion to manage the GEDI team and GEDI CN portfolios	▪ Facilitation of discharge back to place of residence or admission – i.e. appropriate disposition planning	▪ Implement MOC and promote care of the older persons in ED

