#### Study 3: Health economics

Individual patient data will be collected from the Hospital Based Corporate Information System (HBCIS) for Nambour General Hospital. HBCIS is a patient record system for hospital administration that includes information such as patient details, ED presentation complaint, diagnosis, length of stay, bed and menu assignment, discharge status and costs associated with ED episode and inpatient episode of care (if the patient was admitted for inpatient care). For the economic analysis, data will be collected from the two periods in time pre and post GEDI MOC implementation. The historical data during the period of 1^st^ January 2012 – 31^st^ December 2012. The experimental data will be collected for the period of 1^st^ September 2015 to 31^st^ August 2016. While de-identified, the costing data contains sufficient information on hospital resource utilisation such as triage category, length of stay, and treatment received as well as discharge status.

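### Re-presentation is to be modelled with out-of-hospital death as a competing risk, but no source for such deaths is named, and counting only in-hospital deaths makes the mortality comparison depend on place of death

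*Protocol article*

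**What the plan says.** All references are to the protocol article.

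- **Analysis (Study 1, Data analysis).** "We will use survival analysis for ED representations with out-of-hospital mortality as a competing risk". The same section adds: "The survival analyses will use Cox models and we will check the proportional hazards assumption".
- **Variables (Study 1, Data collection).** Death appears twice in the list of outcome variables: as one category of disposition, and as in-hospital death from any cause up to 30 days after the ED presentation. Time to re-presentation is collected within 28 days. The list has no date of death outside hospital.
- **Sources (Study 1, Data collection).** The data come from "linking of the EDIS, HBCIS and financial data providing raw data on all presentations to the ED and those admitted to hospital". Under Study 3, "HBCIS is a patient record system for hospital administration". No death register, community source or aged care facility source is named.
- **Aims (Study aims).** The outcomes are "rates of ED representation within 72 h and 28 days, mortality, ED and hospital LoS" and several others. Neither this list nor the research question under Study design restricts mortality to hospital.
- **Intervention.** The GEDI team's assessment and planning "aim to prevent unnecessary admissions to hospital". Table 1 gives the clinical nurse this task: "Liaison with hospital acute-care substitution services such as the Hospital in The Home and palliative care services". The Discussion describes the model as a substitute for hospital care.

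**The concern.** There are two linked problems.

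First, a competing-risks analysis of re-presentation needs the date of each competing death. The Data analysis section names deaths outside hospital as the competing event. The Data collection section neither lists that variable nor names a source that, as described, would supply it.

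Second, and more serious, the mortality outcome counts deaths only in the place where the intervention tries to have fewer patients. The Background puts admission at about 60% of ED presentations, so a large group already goes home or back to a facility, and GEDI aims to enlarge it. A patient who dies there within 30 days is not an event. If GEDI shifts where people die without changing whether they die, in-hospital mortality falls and a reader of the aims would take this as better survival. Adjustment for age, triage score, season and trend cannot recover deaths that were never recorded.

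**Working it through.** The protocol states no mortality rate, place-of-death split, event count or power on this point, so there is no figure of its own to reproduce. The mismatch comes from setting the sections side by side, as above. The rest is illustration, with assumed inputs marked.

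**A. Mortality**

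Let m be true 30-day mortality, equal in both periods, and let s0 and s1 be the shares of those deaths that occur in hospital before and after GEDI. Observed in-hospital mortality is m × s0 and m × s1, so

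apparent RR = (m × s1) / (m × s0) = s1 / s0,

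which does not depend on m.

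- Assumed 70% to 60%: 0.60 / 0.70 = 0.86.
- Assumed 80% to 75%, 70% or 60%: 0.75 / 0.80 = 0.94; 0.70 / 0.80 = 0.88; 0.60 / 0.80 = 0.75.
- If deaths are counted wherever they occur, the ratio is 1.00 in every case.

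Could such a shift reach significance? The Setting section gives 52,410 presentations a year, 18% of them by people over 70: 52,410 × 0.18 = about 9,434 per period. Treating presentations as independent and unadjusted (a simplification), a two-sided 5% comparison of two proportions gives these chances of a nominally significant false benefit:

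| Assumed true mortality | 80% to 75% | 80% to 70% | 80% to 60% |
|---|---|---|---|
| 5% | 14% | 44% | 96% |
| 10% | 25% | 74% | over 99% |

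The same mechanism can hide harm. With a true RR of 1.10, the apparent RR is 1.10 × s1 / 0.80, that is 1.03, 0.96 and 0.83 for the three shifts.

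**B. Re-presentation**

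Assume constant hazards over 28 days and no true effect on the re-presentation hazard. Let λ = −ln(1 − 0.20) / 28 (20% re-presenting by day 28 in the absence of death, assumed) and μ = −ln(1 − d) / 28, where d is the assumed 28-day risk of death outside hospital. If those deaths are not recorded, the patients stay in the risk set to day 28. The observed proportion re-presenting is

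CIF = λ / (λ + μ) × (1 − exp(−28(λ + μ))),

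and the apparent HR is the ratio of −ln(1 − CIF) between periods.

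- d from 5% to 8%: CIF 0.1951 and 0.1922; −ln(1 − CIF) 0.2171 and 0.2134; apparent HR 0.983.
- d from 3% to 5%: apparent HR 0.989.
- d from 5% to 10%: apparent HR 0.972.

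The estimated cumulative incidence at 72 h or 28 days is the same whether or not the death date is known: a person who died at home did not re-present on either reckoning. What changes is the hazard. Leaving the dead at risk amounts to a subdistribution analysis, not a cause-specific Cox model that removes patients at death.

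**The case against.** The strongest reply has four parts.

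1. **The databases may hold more than is listed.** A reader might infer that EDIS and HBCIS record only in-hospital deaths and that the stated model cannot be run. The documents do not say so. The list covers what will be extracted, and the description of HBCIS under Study 3 is not exhaustive. A full protocol might also name a death source. This stands as a limit on wording: what is established is that no variable or source for out-of-hospital death is named. It does not remove the mismatch, because the article gives an explicit list and explicit sources and then relies on something in neither.

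2. **The plan does not treat deaths at home as successes.** As written, such a death is a competing event, and the mortality variable is openly labelled in-hospital. That is right. Counting those patients as 28 event-free days is what would follow if the dates were missing, not what the plan intends.

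3. **The re-presentation bias is minor.** This stands. A reader might infer that every unrecorded death outside hospital favours GEDI. It does not, because most would be present in both periods. With an assumed 8% mortality and an in-hospital share falling from 70% to 60% or 55%, deaths outside hospital go from 0.08 × 0.30 = 2.4% to 3.2% or 3.6%. Only the difference, 0.8 to 1.2 percentage points, can affect the comparison.

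4. **The mortality figures are all assumed, and in-hospital death is a legitimate outcome.** The first part stands: the stated aims of GEDI make the direction plausible, but they do not prove it, and some patients who go home may be readmitted and die in hospital within the window. The second part does not answer the point. The aims and the research question drop the qualifier, and the intervention acts on the very thing that decides whether a death is counted.

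**Conclusion.** The point holds in two parts of unequal weight.

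The inconsistency between the analysis and the data collection is on the face of the article and must be reconciled. Its numerical effect on re-presentation is likely small: an apparent HR of about 0.97 to 0.99 when the truth is 1.00, under the assumptions in B, with cumulative incidence unaffected.

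The mortality outcome matters more. An in-hospital count cannot separate a change in survival from a change in place of death, and GEDI is designed to change place of care. The apparent RR under no true effect is the ratio of the in-hospital shares: 0.86 for an assumed fall from 70% to 60%, and 0.94 to 0.75 for an assumed fall from 80% to between 75% and 60%. No share is given in the documents, so these show what could happen and do not estimate what will. Nor do the documents designate mortality or re-presentation as safety endpoints. They are listed among the outcomes for testing efficacy, and the problem is that the promised mortality comparison is not the one the listed data would give.

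**What to change.** **Preferred.**

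- Name a linkage to death registration covering both periods, and collect date and place of death.
- Define mortality as death from any cause within 30 days of the ED presentation, wherever it occurs. In-hospital death can remain as a descriptive breakdown.
- State the time origin for re-presentation (arrival or discharge), which the article leaves open, and use death after that origin as the competing event. If time runs from discharge, deaths during the index stay never enter the risk set.

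**If linkage is not available.**

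- Delete the statement that out-of-hospital mortality is a competing risk, and report re-presentation at 72 h and 28 days as cumulative incidence.
- Write in-hospital mortality in the aims, the research question and the conclusions. State that it depends on place of death and is not evidence on overall survival.

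**Cost.** A data-custodian and ethics variation, and some delay while deaths are registered. Extraction is already retrospective from records, so no new contact with patients should be needed. The fallback needs only changes of wording, but it gives up any statement about survival.
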